## **1.2. Rationale for the Study**

Niclosamide is a well-established active substance that is a promising candidate for a repurposing approach to treat COVID-19. Niclosamide is currently marketed as a chewing tablet for the treatment of intestinal worm infections. The marketed formulation is optimized for minimal drug substance absorption. Moreover, absorption levels seem to be highly variable with peaks ranging from 0.76 – 18.3 µM when administering the chewing tablets 2 g QD.

A niclosamide solution has been developed that is expected to release the drug substance more readily and more reproducibly.

This study is primarily designed to investigate pharmacokinetics and safety of single ascending doses of the new oral niclosamide solution. Comparison will be made with the already marketed chewing tablet. A multiple dose part with the niclosamide solution is included to

[figure not shown]

assess the safety and PK after multiple doses of niclosamide solution. The new formulation is being developed to be used in subsequent studies in combination with camostat for the treatment of COVID-19.

### 1.3. Rationale for Dose Selection

The niclosamide treatment regimen against tape worms comprises a 2 g dose at day 1 followed by 6 days of 1 g for individuals aged >6 years. Intestinal resorption is low, and the bioavailability is on average 10% (although there is a high variability).

Part A of the study consists of single ascending doses of the new oral solution with three planned cohorts (A1, A2, A3). The initial dose of 200 mg, in case of assuming 100% absorption, corresponds to the systemic exposure of the chewing tablet of 2000 mg assuming a bioavailability of 10%. However, complete (100%) absorption of the oral solution is highly unlikely since niclosamide is likely to be metabolized already in the intestine. The starting dose of 200 mg is therefore considered safe. The next higher dose of 600 mg is a threefold increase from the starting dose. The final dose of 1600 mg is limited by the solution excipients which are known to give rise to diarrhea at higher volumes. Both the 600 mg and 1600 mg cohorts will only be started if the previous dose is safe and the pre-defined plasma level of above 5  $\mu$ M (approx. 1.6  $\mu$ g/ml) after 8 hours has not been reached. If the 1600 mg dose is not tolerated, there is an option to repeat the cohort with a lower dose of 1200 mg. The last cohort will be repeated under fed conditions to investigate a possible food effect.

The first subject in each cohort will be the sentinel subject receiving an open label niclosamide solution administration.

Overall, the proposed SAD design for this study mimics conventional FIH studies, and thus, seems to be a suitably conservative approach for testing the niclosamide solution formulation.

Part B of the study compares the highest acceptable dose in Part A (1600 mg oral solution) with the highest approved dose of the chewing tablet (2000 mg) given as a QD dosing regimen under fed conditions to determine the relative bioavailability of the new oral solution formulation.

The chosen dose will not exceed the maximum tolerable dose in Part A.

Part C investigate safety and PK of the niclosamide solution over a period of 7 days.

This part consists of three groups: Group 1, 1200 mg niclosamide solution administered once daily, Group 2, 1600 mg niclosamide solution administered once daily and Group 3, placebo.

The medium dose of niclosamide has been added to have the possibility to stop dosing in the 1600 mg group and continue with 1200 mg dosing in case of intolerable side effects, which may occur by accumulation of the excipient PEG-400 in the gut.

Accumulation of niclosamide is not expected after multiple dosing considering the plasma concentration-time profiles observed in Part A of the study.

Niclosamide solution will be administered once daily under fed conditions.

### 1.4. Risk Assessment

The risks of the treatment is limited in the sense that investigational substance, niclosamide, has been marketed and used for decades and have thus an established safety profile. The risks in the study derive from using niclosamide as solution which most probably lead to an increase of the plasma concentration of niclosamide.

Niclosamide chewing tablets has been approved for the treatment of tapeworm infection for more than 50 years. The highest approved dose of niclosamide is 2000 mg on day 1, followed by 1000 mg/d up to seven days.

[figure not shown]

According to the SmPC of niclosamide chewing tablets (SmPC, Yomesan®), the following adverse drug reactions are known from spontaneous reporting: Hypersensitivity reactions (e.g. erythema, pruritus, and exanthema), dizziness, cyanosis, gastrointestinal symptoms such as such as nausea, retching, abdominal pain and diarrhea. The healthy volunteers will be monitored closed about these expected adverse events.

Overall, doses up to 2000 mg niclosamide chewing tablets were safe and well tolerated.

The potential risk of the niclosamide solution will be minimized by a SAD design in Part A of the study, which is comparable with a FIH study. The initial dose is low and will only be increased to the next higher dose after reviewing the safety and PK data by a SMC.

The risk to subjects in this 3-part study will be minimized by adherence to the inclusion/exclusion criteria and close clinical monitoring as well as attention to adverse effects throughout the trial. Safety will be monitored by safety lab, vital signs, physical examination, ECG and recording of adverse events.

For a detailed benefit/risk assessment please see Investigator's Brochures of niclosamide

## **1.5. Risk Assessment on COVID-19 Pandemic and Risk Mitigation Measures**

As for the general population, there is a potential risk of a severe acute respiratory syndrome coronavirus type 2 (SARS-CoV-2) infection for study participants as long as the COVID-19 pandemic continues. In order to avoid the inclusion of SARS-CoV-2 infected subjects and to minimize the potential infection risk during study participation, only proven SARS-CoV-2 negative participants without any symptoms of a respiratory disease will be included into the study (see Section 4.3 Exclusion Criteria). During the entire study, all recommendations issued by authorities and local guidelines with respect to minimizing the risk of disease spreading, e.g. social distancing, disinfection, strict hygiene measures, and wearing of mouth-nose masks shall be followed. Details are described in a separate document provided to the EC and BfArM. All participants will be closely monitored for signs and symptoms of COVID-19 during the entire study duration. Study treatment will be immediately terminated for study participants with a SARS-CoV-2 infection or with contact to SARS-CoV-2 positive subjects. All respective subjects will be clinically followed-up according to the recommendations issued by local regulations. During the pandemic situation, further measures according to recommendations and requirements from local health authorities may become necessary and will be followed within the context of this study as far as applicable in order to ensure full implementation of the principles of GCP with priority on subject safety in this study also during the COVID-19 pandemic situation.

## **2. Study Objectives and Endpoints**

### **2.1. Objectives**

#### **2.1.1. Primary Objectives**

- To assess the safety and tolerability of single ascending doses of the niclosamide solution in healthy volunteers (Part A)
- To assess PK parameters of single ascending doses of the niclosamide solution in healthy volunteers (Part A)

### 2.1.2. Secondary Objectives

- To assess the PK of a single dose of the niclosamide solution under fed and fasted conditions in healthy volunteers (Part A)
- To assess saturation and/or dumping effects of niclosamide solution by dose escalation (Part A)
- To assess the relative bioavailability of the niclosamide solution compared to the already marketed chewing tablet administered as single dose under fed conditions in healthy volunteers (Part B)
- To assess the safety and PK of the niclosamide solution after multiple oral doses under fed conditions in healthy volunteers (Part C)

## 2.2. Endpoints

### 2.2.1. Primary Endpoints

Safety:

- Adverse event monitoring - AEs and SAEs
- Physical examination
- Vital sign monitoring (blood pressure, pulse rate, respiratory rate)
- ECG
- Safety lab

Single dose PK Parameters:

- $C_{max}$ ,  $C_{12h}$ ,  $C_{24h}$ ,  $T_{max}$ ,  $AUC_{last}$ ,  $AUC_{inf}$ ,  $T_{1/2}$ ,  $CL/F$

### 2.2.2. Secondary Endpoints

Food effect and saturation and/or dumping effects:  $C_{max}$ ,  $T_{max}$ ,  $AUC_{last}$ , and others if deemed appropriate.

Multiple dose PK Parameters:

$C_{maxss}$ ,  $T_{maxss}$ ,  $AUC_{tau, ss}$ ,  $CL/F_{ss}$ ,  $T_{1/2}$

Others may be added if deemed necessary.

## 3. Investigational Plan

### 3.1. Study Design

The study consists of three parts:

- Part A is a randomized, double-blinded, placebo-controlled, single ascending dose (SAD) study with 3 cohorts (N= approximately 12 subjects)
- Part B is a randomized, open-label, two time two-sequence, two-period crossover study to investigate the relative bioavailability of the new niclosamide solution compared to the marketed chewing tablets as single dose under fed conditions (N= approximately 4 subjects in a crossover design)
- Part C is a randomized, double-blinded, placebo-controlled multiple dose study investigating safety and PK of the niclosamide solution (N= approximately 12 subjects).

For all three parts, each subject will participate in a screening period during which a full physical examination, medical history, vital signs, ECG evaluation and safety laboratory tests evaluation will be performed.

### Part A: Single ascending dose (SAD)

Four subjects per cohort will be randomized to receive a single oral dose of the niclosamide solution or matching placebo in a 3:1 ratio.

The SAD cohorts are planned as follows:

*Cohort A1:* 200 mg (fasted conditions)

*Cohort A2:* 600 mg (fasted conditions)

*Cohort A3:* 1600 mg (fasted and fed conditions)

Dose escalation will only be performed with the niclosamide solution if the previous dose was safe and the plasma concentration of above 5µM after 8 hours has not been reached in all subjects in a cohort. If the 1600 mg is not tolerated there is an option to decrease the dose to 1200 mg niclosamide solution.

The last dose cohort (A3) will be repeated in the same subjects under fed conditions. The subjects will be dosed under fed conditions if the cohort A3 under fasted condition is safe and well tolerated (based on 48 hrs safety data) and PK data is available.

**Figure 1 Study Design SAD Part**

[figure not shown]

### Criteria for dose escalation in SAD

A safety monitoring committee (SMC) will continuously monitor subject safety and take decision on dose escalation.

### Sentinel dosing in SAD

In each cohort, the first subject will be the sentinel subject receiving an open-label niclosamide solution administration. Safety and tolerability data for this subject up to 24 hrs after dosing will be evaluated by the Investigator and sponsor and if there are no clinically relevant safety or tolerability findings, the remaining 3 subjects within the same cohort will be dosed.

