| Design, Dosage and Administration | 
This study consists of three parts:
 
Part A is a randomized, double-blinded, placebo-controlled, single ascending dose (SAD) study with 3 planned cohorts.
 
In total 4 subjects will be enrolled in each cohort (ratio 3:1, verum : placebo).
 
Planned single oral doses are:
 
Cohort A1: 200 mg (fasted conditions)
 
Cohort A2: 600 mg (fasted conditions)
 
Cohort A3: 1600 mg (fasted and fed conditions)
 
Dose escalation will only be performed with the new oral solution if the previous dose was safe and the plasma concentration of 5µM (approx. 1.6 µg/ml) after 8 hours has not been reached in both subjects. If the 1600 mg is not tolerated there is an option to decrease the dose to 1200 mg niclosamide solution.
 
Cohort A3 will be repeated in the same subjects under fed conditions if the administration under fasted conditions is safe and well tolerated.
 
Part B* consists of one randomized, open-label, two-sequence, two-period crossover cohorts comparing the new niclosamide solution with the marketed chewing tablets.
 
Cohort B compares a single dose of the highest dose that was tested to be safe and tolerable in part A with the marketed chewing tablet in the approved dose of 2000 mg.
 
Approximately 4 subjects will be enrolled in this part
 
Cohort B
 

Sequence	Period 1	Period 2	

1 (n=2)	Solution 1600mg under fed conditions	Chewing tablet 2000 mg under fed conditions	

2 (n=2)	Chewing tablet 2000 mg under fed conditions	Solution 1600 mg under fed conditions	

 | Sequence                                    | Period 1 | Period 2 | 1 (n=2) | Solution 1600mg under fed conditions | Chewing tablet 2000 mg under fed conditions | 2 (n=2) | Chewing tablet 2000 mg under fed conditions | Solution 1600 mg under fed conditions |

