Placebo-control: A placebo control is included in cohorts A and C that may allow to differentiate between drug-related AEs and AEs which might occur in the absence of active treatment.

Food effect: The last cohort in Part A will be repeated under fed conditions. It is expected that food influences the systemic exposure of niclosamide solution formulation.

MD design of Part C: A MD design was chosen to obtain safety and PK data over a treatment period which is comparable with the treatment period in COVID-2 infected patients.

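### Part A is described as randomised 3:1 and double-blind for all four subjects per cohort, but the first of the four is an open-label niclosamide sentinel, so only three can be randomised and blinded, at 2:1

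*Protocol*

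**What the plan says.** The design list in Protocol section 3.1 states: "Part A is a randomized, double-blinded, placebo-controlled, single ascending dose (SAD) study with 3 cohorts (N= approximately 12 subjects". The Part A paragraph of the same section adds: "Four subjects per cohort will be randomized to receive a single oral dose of the niclosamide solution or matching placebo in a 3:1 ratio". The synopsis gives the same split: "In total 4 subjects will be enrolled in each cohort (ratio 3:1, verum : placebo". Section 8.1 again presents 3:1 as the randomisation ratio for the four subjects of a cohort.

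Three further places describe randomisation or blinding without any exception. The visit description in section 3.1 has subjects randomised to niclosamide or placebo. Section 6.2 randomises eligible subjects on Day -1 and hands out numbers in sequence. Section 6.3 says that Parts A and C are randomised and meant to be double-blind against placebo.

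The sentinel paragraph of section 3.1 says that in each cohort "the first subject will be the sentinel subject receiving an open-label niclosamide solution administration". Section 1.3 repeats this: "The first subject in each cohort will be the sentinel subject receiving an open label niclosamide solution administration". If the sentinel's 24-hour data raise no concern, "the remaining 3 subjects within the same cohort will be dosed". One sentinel plus three others makes four, so the sentinel belongs to the cohort and is not an addition to it.

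Section 3.2 gives the purpose of the placebo control in Parts A and C as one "that may allow to differentiate between drug-related AEs and AEs which might occur in the absence of active treatment". Section 8.2 analyses subjects by the treatment they received.

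**The concern.** A subject whose treatment is fixed in advance and given open-label is neither randomised nor blinded. The protocol therefore gives Part A a property that one subject in four does not have, and nowhere says how the other three are allocated.

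Safety and tolerability in Part A is a primary objective (section 2.1.1), and placebo is there to help separate drug effects from background events. The adverse reactions listed for niclosamide in section 1.1 include nausea, abdominal pain and diarrhoea, several of which depend on what the subject reports. The investigator assigns relatedness (section 7.2.2), and relatedness also enters the safety stopping rules in section 3.3. For the sentinel, both the reporting and the judgement are made with the treatment known. In cohort A3 this extends to the fed period, because the same subjects are dosed again.

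**Working it through.** There is no power calculation to reproduce; the check is a count.

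**Inputs**
- 3 cohorts of 4 subjects, 3 active to 1 placebo (synopsis, sections 3.1 and 8.1).
- 1 open-label niclosamide sentinel per cohort, counted among the four (sections 1.3 and 3.1).

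**The plan's own figure**
- Total: 3 × 4 = 12.
- Active: 3 × 3 = 9. Placebo: 3 × 1 = 3.
- The stated size of about 12 and the ratio of 3:1 are reproduced.

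**Taking the sentinel out, per cohort**
- Left to randomise: 4 − 1 = 3.
- Active among them: 3 − 1 = 2. Placebo: 1. The ratio is 2:1.
- This is the only split of the remaining three that keeps 3 active and 1 placebo in the cohort.

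**Over three cohorts**
- Randomised and blinded: 3 × 3 = 9, of whom 3 × 2 = 6 receive niclosamide and 3 × 1 = 3 receive placebo.
- Open-label and not randomised: 3 × 1 = 3, all on niclosamide.
- Check: 6 + 3 + 3 = 12.

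**Share of active data that is unblinded**
- At each dose: 1/3 = 33%. Over Part A: 3/9 = 33%.

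**Can the two rules both be followed as written?** If all four subjects were truly randomised 3:1, the first would draw placebo with probability 1/4 in each cohort. The chance of this in at least one of three cohorts would be 1 − 0.75³ = 0.578. This shows only that the two statements are incompatible; it does not predict how the list was built.

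**The case against.** The strongest reply is that the design is disclosed. The sentinel rule appears twice, section 3.2 gives a rationale for it, and a careful reader would let the specific rule override the general one. On that reading 3:1 remains true of treatment received, and no dose, enrolment number or escalation rule changes. This stands. It shows that the wrong element is the label of randomised and double-blind for all four subjects, not the sentinel. Figure 1, which shows the Part A design, is not available here and may show the sentinel separately.

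Stronger readings are tempting, and the documents do not support them.

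- A reader might infer that a sentinel could have been given placebo. Nothing describes how the list treats the first number, and two sections state outright that the sentinel receives niclosamide.
- A reader might infer a biased 9 v 3 comparison of all active subjects with placebo. Section 8.1 provides only for pooling placebo, where appropriate; no pooling of active subjects across doses is planned. The issue therefore applies within each dose group.
- A reader might cite section 6.3 for four subjects at 3:1. It states only randomisation and blinding; the numbers come from sections 3.1 and 8.1.
- A reader might treat the bias as established. It is a possibility of unknown size, in a descriptive analysis with no hypothesis test and few placebo subjects. Plasma concentrations are measured by assay and should hardly depend on who knows the treatment.

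It is also fair to say that table layouts belong in the separate statistical analysis plan, that section 8.1 already promises listings of all subject data, and that Amendment 2 was written after Part A had been evaluated. Rewording cannot alter how Part A was run. It can still determine how Part A is described and reported.

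**Conclusion.** The inconsistency is real and minor. Sections 3.1, 6.2, 6.3 and 8.1 describe Part A subjects as randomised or blinded without exempting the sentinel, while sections 1.3 and 3.1 make one subject per cohort open-label niclosamide. At most 9 of 12 subjects can be randomised and blinded, as 6 niclosamide v 3 placebo, with 3 open-label sentinels beside them.

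The 2:1 and 6 v 3 figures are derived, not stated. They assume that each cohort keeps three active subjects and one placebo subject including the sentinel, that all three cohorts run, and that there are no replacements and no additional 1200 mg cohort.

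One third of the active adverse event data at each dose is collected unblinded, which may bias the descriptive comparison with placebo; the direction and size cannot be worked out from the protocol. The pharmacokinetic conclusions are not in question.

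**What to change.** Keep the sentinel and reconcile the passages. Describe each Part A cohort as one open-label niclosamide sentinel, not randomised, plus three subjects randomised 2:1 to niclosamide or placebo under double-blind conditions. State the sentinel's exemption in sections 3.1, 6.2, 6.3 and 8.1, and present 3:1 as the ratio of treatments received, not as the randomisation ratio.

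In the Part A report, identify the sentinels and give adverse event summaries by dose against placebo twice, with and without them. State that 9 subjects were randomised and blinded, not 12, once this has been checked against the allocation actually used.

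The cost is a few sentences and one additional adverse event table. It needs no new data and changes no dose or clinical rule.

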### SAD Part visits design:

Part A of this study is comprised of a screening visit (between Day -21 and -2), a baseline visit (Day -1), a treatment visit with a single dose of niclosamide solution or placebo (Day 1), and an End of Study (EOS) visit (between Day 4 and 6).

Subjects will remain domiciled in the study site from Day -1 until the Day 2 (24h post dose) and until assessments have been completed. Subjects will be allowed to leave the study center on Day 2 (safety signals, if any, are expected to occur within 24h from the drug administration, due to the expected short half-life of niclosamide solution) at the discretion of the Investigator, if there are no prohibitive safety findings. The subjects will be asked to return to the study site for the EOS assessments on Day 4 (+2 days). The EOS evaluation has also to be performed if a subject prematurely terminates the study for any reason.

All baseline safety evaluations results must be available prior to dosing. Subjects will fast  $\geq 9$  hours overnight between Day -1 and Day 1 pre-dose and remain fasted 4 hours post-dose on Day 1. Subjects will be randomized to receive either the niclosamide solution or matching placebo, depending on the randomization assignment.

Cohort A3 will be repeated in the same subjects under fed conditions (high fat breakfast). The subjects will be dosed under fed conditions as soon as the PK is available and safety data for 48 hrs, however not shorter than 5 half-lives based on the PK results of cohort A3 fasted conditions.

### Part B relative bioavailability evaluation

Part B will only be initiated after approval from Ethics Committee and Competent Authority via a substantial amendment, along with the relevant PK, and safety data from the niclosamide solution from Part A.

Part B focus on the bioavailability of the new niclosamide solution compared to the marketed chewing tablets. Based on the PK-results of Part A, Part B will be performed under fed conditions.

This approach compared a single dose of the oral solution of the highest dose that was tested to be safe and tolerable in Part A with the marketed chewing tablet in the approved dose of 2000 mg under fed conditions.

Approximately 4 subjects will be enrolled in Part B.

#### Cohort B1:

| Sequence | Period 1                                             | Period 2                                           |
|----------|------------------------------------------------------|----------------------------------------------------|
| 1 (n=2)  | Solution 1600mg  QD under fed conditions | Chewing tablet 2000 mg QD under fed conditions     |
| 2 (n=2)  | Chewing tablet 2000 mg QD under fed conditions       | Solution 1600  QD under fed conditions |

 highest dose that was tested to be safe and tolerable in Part A.

Each subject will participate in a 21-day screening period, one treatment period with a wash out period of 1 day and an EOS visit (between Day 6 and 8). The wash-out phase might be increased to 2 days depending on  $T_{1/2}$  in early cohorts. The washout phase will be at least 5 times  $T_{1/2}$  based on the PK results of Part A.

Subjects will remain domiciled in the study site from Day -1 until the Day 4 (24h post dose) until the safety assessments have been completed. Subjects will be allowed to leave the study center on Day 4 (safety signals, if any, are expected to occur within 24h from the drug administration, due to the expected short half-life of niclosamide solution) at the discretion of the Investigator, if there are no prohibitive safety findings. The subjects will be asked to return

[figure not shown]

to the study site for the EOS assessments on Day 6 (+2 days). The EOS evaluation has also to be performed if a subject prematurely terminates the study for any reason.

All baseline safety evaluations results must be available prior to dosing.

